## Abstract

Numerous studies have shown the efficacy of smoking cessation interventions. However, some challenges, such as relapse rates, remain. The availability of information technologies (ICTs) offers promising opportunities to address such challenges. The aim of this paper is to describe the protocol followed to assess the efficacy of a face-to-face cognitive–behavioral intervention for smoking cessation using a smartphone application as a complement, compared with a control group. A single blind, two-arm, randomized controlled trial is proposed (NCT04765813). The participants will be smokers over 18 years old, who smoke at least eight cigarettes per day. Participants will be randomized to one of two conditions, using a 1:1 allocation ratio: (1) cognitive–behavioral smoking cessation treatment along with an App with active therapeutic components (*SinHumo* App); or (2) cognitive–behavioral treatment along with the use of a control App (without active components). The experimental App will be used during the eight treatment sessions and for 12 months after the end of treatment. The primary outcome measures will be 7-days point-prevalence abstinence at 12-months follow-up. We expect the experimental App to obtain higher abstinence rates at the end of treatment and at one-year post-treatment follow-ups and lower relapse rates, compared to the control App.

## 1. Introduction

Smoking remains the leading avoidable cause of disability, mortality, and morbidity worldwide [1], and it is responsible for more than 8 million deaths around the world every year [2]. Despite the consistent evidence demonstrating that tobacco use is a significant health-related risk factor, 28% of adults smoked in the European Region in 2020 [2], constituting a significant public health concern. The most common health complications related to smoking are cancer, respiratory disease, and cardiovascular disease [3]. Smoking is also associated with certain mental disorders, such as anxiety, depression, and schizophrenia [4]. In addition, smoking related diseases lead to significant health care costs, accounting for 5.7% of global health care expenditure, which shows the huge economic impact of smoking worldwide [5].

Psychological treatments (i.e., cognitive–behavioral approaches, behavioral counseling) for smoking cessation are first-line treatments that have proven efficacy to quit smoking among different populations [6]. A systematic review carried out by Stead et al. [7] concludes that group behavioral interventions for smoking cessation, when compared to self-help programs, brief advice, or no intervention, obtain better results, with a risk ratio (RR) of 1.88, 1.25, and 2.6, respectively. However, some challenges remain, such as treatment accessibility [8] or relapse rates after quitting [9,10]. In fact, a significant percentage of smokers who achieve abstinence relapse within weeks or months of completing treatment [11]. Some studies show that twelve months after the end of a smoking cessation treatment, relapse rates are found to be 70% in psychological interventions [12], and around 80% in pharmacological interventions [10].

Nowadays, the availability of information technologies (ICTs) (i.e., the Web, smartphones) offers promising opportunities to address such challenges. The use of ICTs in the field of health has grown and developed significantly, demonstrating their utility in several areas, such as diabetes management, health-promoting behaviors (i.e., physical activity), or mental health [13,14]. For instance, in a systematic review, Erbe et al. [15] concluded that Internet-based interventions to support face-to-face treatment for adults with mental disorders decrease the likelihood of treatment dropout, help maintain therapeutic changes, and increase abstinence rates in people with substance use disorders.

In this context, the use of mHealth (mobile health) is becoming increasingly promising. mHealth is defined as the use of mobile devices, such as mobile phones or personal digital assistants (PDA), as a means to support or deliver health-related services [16]. Specifically, in recent years, a major development of smartphone Apps for health promotion and maintenance has been observed along with the rapid increase of mobile phone ownership and usage worldwide [17]. These advances can also be seen in the field of psychological intervention with the development of smartphone apps that target different problems and mental disorders. For instance, several studies have suggested that using a mobile App to complement face-to-face interventions addressing addictive disorders could improve abstinence outcomes [18]. In fact, a study conducted by Gustafson et al. [19], comparing the efficacy of two cognitive–behavioral treatments for alcohol consumption (with and without the use of an App), found positive outcomes during the eight months of the intervention and the four-months follow-up in the App condition. It was also considered that the use of Apps could be useful as an adjunct to psychological smoking cessation treatment [20]; in particular, to achieve abstinence and prevent relapse [21,22].

mHealth Apps for smoking cessation are being widely developed, and although they offer promising results, they are still modest [23]. These Apps can be classified as standalone general apps for smoking cessation without any face-to-face contact with health-care professionals, or smoking cessation apps that are designed to be used as a complement to face-to-face intervention [21]. Recent reviews point out that smoking cessation apps combined with face-to-face intervention improve abstinence outcomes [24]. However, the most increased development has been for standalone self-help Apps, and scarce studies have been conducted to assess the efficacy of a face-to-face treatment combined with an App compared to face-to-face treatment alone. Additionally, recent systematic reviews have highlighted the need for well-powered randomized controlled trials to examine the efficacy of smoking cessation apps [21,25]. Therefore, examining whether using a mobile App with a face-to-face psychological smoking cessation treatment could improve abstinence outcomes is warranted.

The main aim of the present randomized controlled trial is to examine whether the SinHumo smartphone application (iOS and Android), used as a complement of a face-to-face cognitive–behavioral smoking cessation treatment, improves smoking cessation rates at the end of treatment, and at 3-, 6-, and 12-months follow-up, compared with a control group which receives the same smoking cessation treatment and a control App (without active components). The main hypothesis is that combining a cognitive–behavioral psychological treatment to quit smoking and an App with active therapeutic components will obtain higher abstinence rates at the end of treatment and the 12-month follow-up period and lower relapse rates compared to the control group.

## 2. Materials and Methods

### 2.1. Research Design

The proposed study is a two-arm, single-blind, randomized controlled trial (NCT04765813) to assess the efficacy of a cognitive–behavioral intervention for smoking cessation complemented by an App. The overall study design is summarized in Figure 1.

### 2.2. Recruitment

Participants will be recruited through the media, publications on the Smoking Cessation Unit’s social networks (Facebook and Instagram), posters in health-care centers, word of mouth, or referred to the Unit by their primary care physician or other specialized services of the health-care system. Independently of their origin (patients referred by their primary care physician, word of mouth, or social media), all potential participants have to personally contact the trial staff by telephone or email. Before participants enroll in the study, written informed consent will be obtained. Then, the different phases of the study (assessment, treatment, and follow-ups) will be carried out.

### 2.3. Participants

Sample size calculation was performed using the software developed by Wang and Ji [26]. To detect a 20% difference (50% abstinence in the experimental group vs. 30% in the control group) between conditions at the 12 months follow-up (90% power at an alpha of 0.05), a minimum of 99 participants per group will be required. With an estimated attrition of 25%, 264 participants (132 per group) are required.

To be included in the study, participants should meet the following inclusion criteria: (1) 18 years of age or older; (2) smoke at least six cigarettes per day; (3) desire to participate voluntarily in the smoking cessation treatment; (4) correctly fill out all the pre-treatment assessment questionnaires; (5) able to provide written informed consent; (6) currently own a valid email address; and (7) having a smartphone with an Internet connection (Android or iOS) and being willing to use it during treatment.

Exclusion criteria include: (1) having a diagnosis of a severe mental disorder (bipolar disorder and/or psychotic disorder); (2) having a substance use disorder (alcohol, cannabis, cocaine, heroin), different from a tobacco use disorder; (3) smoke rolling tobacco, snuff, cigars, little cigars, or other tobacco products (i.e., e-cigarettes); (4) have participated in an effective psychological treatment to quit smoking during the previous 12 months; (5) have received an effective pharmacological treatment to quit smoking in the previous 12 months (nicotine gum or patches, bupropion, varenicline); (6) have a physical pathology involving life-threatening risks for the person which would require immediate intervention in an individual format (e.g., recent myocardial infarction, pneumothorax); and (7) have a visual impairment that impedes the use of the App.

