#### 2.7.1. Primary Outcome

The primary outcome was the self-reported seven-day point prevalence of complete smoking abstinence (“not even a puff”) at 12-months follow-up. 

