### 2.11. Statistical Analysis

A descriptive analysis to summarize the characteristics of the total sample will be conducted. Comparisons between the two groups will be performed using an independent sample *t*-test for continuous variables (i.e., number of cigarettes smoked per day) and a chi-squared test for categorical variables (i.e., smoking status). Logistic regression analyses adjusted for baseline characteristics (i.e., sex, age, education level) will be carried out to examine whether abstinence rates differ significantly between conditions at the end of treatment, and at 3-, 6-, and 12-months follow-up. Mediation analysis will be conducted to analyze the role of different variables (i.e., depressive symptoms) in the relationship between treatment condition and smoking status. Multilevel and survival analysis will also be carried out to examine the relapse process. All data analysis will follow the intention-to-treat principle, which includes in the primary analysis all randomized participants [45]. A *p* value < 0.05 will be considered statistically significant.

The study results will be reported following the Consolidated Standards of Reporting Randomized Trials of Social and Psychological Interventions (CONSORT-SPI 2018) statements [46,47].

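### The 99 per group for 90% power fits only a one-sided 0.05 test; the tests as written are two-sided and have about 82–84% power at that size

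*Protocol article*

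**What the plan says.** Section 2.3 (Participants) of the protocol article sizes the trial on "50% abstinence in the experimental group vs. 30% in the control group" at 12 months, and concludes: "90% power at an alpha of 0.05), a minimum of 99 participants per group will be required". It then allows for losses: "With an estimated attrition of 25%, 264 participants (132 per group) are required". The Abstract gives equal allocation ("using a 1:1 allocation ratio"). The endpoint is binary: Section 2.7.1 names the "self-reported seven-day point prevalence of complete smoking abstinence" at 12 months.

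Section 2.11 (Statistical Analysis) lists, for comparing the groups, "a chi-squared test for categorical variables (i.e., smoking status"), and an adjusted logistic regression "to examine whether abstinence rates differ significantly between conditions at the end of treatment" and at the three follow-ups. The only decision rule is that a p "value < 0.05 will be considered statistically significant".

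Neither section says whether alpha is one- or two-sided.

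**The concern.** A sample size of 99 per group is small for a 20-point difference from 30% at 90% power. The attrition step is correct, so attention falls on the alpha. If the calculation spent the whole 5% in one tail while the analysis splits it over two, the sample size and the analysis use different error rates, and the planned tests do not have the stated power.

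This is the only power statement for the primary outcome, and the Introduction justifies the trial partly by the lack of well-powered trials in the field. A reader of a null result would take the trial to have had a 10% chance of missing a 20-point effect, when on the plan's own basis the chance is about 17%. An undeclared sidedness also leaves room to choose a one-sided test once results are known. That would double the false-positive rate in favour of the App from 2.5% to 5%.

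**Working it through.** **Inputs.** p₁ = 0.50, p₂ = 0.30, difference 0.20, power 90%, alpha 0.05, n = 99 per group and attrition 25% (all Section 2.3); 1:1 allocation (Abstract). Normal quantiles: 1.645 for one-sided 0.05, 1.960 for two-sided 0.05, 1.282 for 90% power.

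**Step 1: reproduce the plan's figure.** The unpooled formula is

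n = (z_α + z_β)² × [p₁(1−p₁) + p₂(1−p₂)] / (p₁−p₂)²

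The variance term is (0.25 + 0.21) / 0.04 = 11.5.

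- One-sided 0.05: (1.645 + 1.282)² × 11.5 = 98.5, rounded up to **99**. This is the plan's number.
- Attrition: 99 / 0.75 = **132** per group, 264 in total. This also matches.

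**Step 2: the same calculation, two-sided.**

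- Unpooled: (1.960 + 1.282)² × 11.5 = 120.8, rounded up to **121**.
- Pooled variance under the null (mean rate 0.40): [1.960 × √0.48 + 1.282 × √0.46]² / 0.04 = 124.0, so **124**.
- Other two-sided variants give more: arcsine 125, simple pooled 127, log odds ratio 129, continuity-corrected 134. None gives 99.

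**Step 3: power at 99 per group.** With the unpooled standard error √(0.46/99) = 0.0682, two-sided power is Φ(0.20/0.0682 − 1.960) = Φ(0.974) = 83.5%. With the pooled standard error under the null, √(0.48/99) = 0.0696, it is Φ[(0.20 − 1.960 × 0.0696)/0.0682] = Φ(0.932) = 82.4%.

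| Method, n = 99 per group | One-sided 0.05 | Two-sided 0.05 |
|---|---|---|
| Unpooled | 90.1% | 83.5% |
| Pooled | 89.5% | 82.4% |
| Exact enumeration of the uncorrected chi-squared test | 89.2% | 82.6% |
| Exact enumeration with continuity correction | 86.3% | 78.5% |

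By the pooled and unpooled formulas the shortfall from 90% is 6.5 to 7.6 points.

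**Step 4: what 90% two-sided power would take.** It needs 121 to 124 evaluable per group, which is 22% to 25% more than 99. With 25% attrition this is 121/0.75 = 161.3 and 124/0.75 = 165.3, so 162 to 166 randomised per group against the 132 planned. Put the other way, 99 per group gives 90% two-sided power for a difference of about 22 to 22.5 points from a 30% control rate (at 22 points, 88.8% pooled and 89.8% unpooled; at 22.5 points, 90.1% pooled).

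**Step 5: sensitivity to who is analysed.** Section 2.11 puts all randomised participants in the primary analysis.

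- If all 132 per group have outcomes and the rates are still 50% and 30%, two-sided power is 91.7% to 92.3%.
- If the 25% lost were counted as smokers (an assumption; the article gives no such rule), the rates become 0.75 × 50% = 37.5% and 0.75 × 30% = 22.5%, and two-sided power at 132 per group is about 76%.

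**The case against.** The article never says two-sided, its hypothesis is directional (higher abstinence with the App), and under a one-sided 0.05 test the 90% is arithmetically right. An analysis plan not shown here might state the sidedness. What stands is that the two-sided reading is an inference. It is a firm one: the chi-squared test on a 2×2 table has no direction, the regression asks whether rates differ, and the p-value threshold is unqualified. A directional expectation does not make a test one-sided. If a one-sided test was intended, Section 2.11 does not describe it, so the two sections still disagree.

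A second objection is that the intention-to-treat analysis covers 132 per group, where power could be about 92%. That holds only if nobody is lost or the losses leave the rates unchanged. Section 2.3 ties its 90% to 99 and adds a third more participants precisely because it expects losses, and counting the lost as smokers gives about 76% instead. So 82–84% is the corrected value of the plan's own calculation, conditional on 99 analysed per group. It is not a forecast for every way of handling missing outcomes.

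Third, the analysis named for abstinence rates is an adjusted logistic regression, for which the chi-squared figure is only an approximation. That is fair, but it does not restore 90%: the unadjusted log odds ratio calculation gives 81.3% at 99 per group.

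Finally, the correction changes one figure and no conduct, and power stays above 80% on the plan's own basis. That makes the correction cheap, but the stated figure is still wrong for the tests described.

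**Conclusion.** The concern holds. The 99 per group in Section 2.3 rests on an undisclosed one-sided alpha of 0.05, and the tests described in Section 2.11 are two-sided as written. On the plan's own basis of 99 per group at 50% against 30%, power is about 82–84%, not 90%, and the type II error is about 17%. The conclusion assumes that an unqualified p < 0.05 with a chi-squared test means two-sided, and that the chi-squared test is run without continuity correction; with the correction, power falls to about 78.5%. The attrition step is correct.

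**What to change.** Keep 264 participants and restate Section 2.3 along these lines: *With 99 evaluable participants per group, a two-sided 5% chi-squared test has about 82–83% power to detect 50% against 30% abstinence at 12 months; allowing for 25% attrition, 132 per group will be randomised.* State in Section 2.11, and in any separate analysis plan, that the tests are two-sided at 5%. Add that the figure is for the unadjusted comparison and approximates the power of the adjusted regression.

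Do not declare a one-sided 0.05 test to keep the 90%. Enrolment was already under way when the article was written (Section 2.10), and such a change would loosen the false-positive rate in the App's favour.

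The cost is a sentence in each section and a less favourable stated power. No extra participants are needed. Keeping 90% two-sided power on the same basis would instead mean 162 to 166 randomised per group, 324 to 332 in total.

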### 2.4. Treatment Interventions

#### 2.4.1. Cognitive Behavioural Smoking Cessation Intervention and SinHumo App (Experimental Condition)

This intervention is a multicomponent cognitive–behavioral treatment (“Programa para Dejar de Fumar”) [27], which has been manualized and used in different contexts (i.e., hospitals, private companies) in Spain. The description of the main intervention has been previously published [28,29]. The main therapeutic components are: (1) treatment contract; (2) self-report and graphic representation of cigarette consumption; (3) information about tobacco; (4) nicotine fading (gradual reduction of nicotine and tar ingestion); (5) stimulus control; (6) activities to prevent withdrawal syndrome; (7) relapse prevention strategies (including assertion training, problem-solving training, changing tobacco-related misconceptions, management of anxiety and anger, exercise, weight control, and self-reinforcement); and (8) components of Behavioural Activation (BA), including an analysis of the relationship between behavior and mood, identifying situations and behaviors that decrease mood, identifying avoidance behaviors, identifying rumination and worry, self-reporting pleasant daily activities, pleasant activity scheduling to increase engagement in rewarding activities, and reducing patterns of behavioral avoidance (Table 1). 

This intervention is applied in a group format and consists of 8 one-hour sessions once a week. Due to the COVID-19 pandemic, these sessions will be conducted through video calls (i.e., Microsoft Teams).

Along with the intervention, participants will be provided with an App with active therapeutic components, which will be used during the treatment sessions (Phase 1) and the follow-up period (Phase 2):

-During Phase 1 (Table 1), the App will have the following content: smoking self-monitoring tool, cigarettes consumption graph, a list of personal reasons to quit smoking, setting weekly cigarette reduction goals tool (to nicotine fading), stimulus control tool (set weekly non-smoking situations), deep breathing videos, self-monitoring of BA activities tool, inter-session motivational and weekly reinforcement notifications of goal achievements, and access to the written materials in pdf format provided during the face-to-face sessions (Figure 2).-During Phase 2 (Table 2), the App content will differ depending on the participants’ smoking status, which are defined as follows: (a) abstinents, as those participants who report being abstainers; (b) relapsed, as those participants who report abstinence at the end of treatment, but who relapsed during the follow-up period; and (c) smokers, as those participants who never quit smoking during treatment and follow-ups. The specific components are detailed below:
(a)*Abstinent*: gains and achievements made since quitting smoking (number of days without smoking, saved money, time gained, and physical improvements), behavioral and cognitive recommendations for abstinence maintenance, strategies for coping with cravings (distraction tools, such as gifs, games, or videos; and social-support-seeking strategies, such as access to an emergency contact list), motivational strategies (list reasons to remain abstinent, personal video recording focused on reasons for quitting, and videos of close friends/relatives motivating them to remain abstinent), access to the materials in pdf format that were provided during the sessions, and the possibility of self-reporting tobacco use if a lapse or relapse occurs (Figure 3). Likewise, they will receive notifications during this follow-up phase according to gains and achievements as they remain abstinent through the one-year follow-up.(b)*Relapsed*: behavioral and cognitive advice to quit (tips), the possibility of setting a new quit date in a calendar, strategies to cope with cravings (distraction tools, such as gifs, games, or videos; and social-support-seeking strategies, such as access to an emergency contact list), motivational strategies (list of personal reasons for quitting, personal video with reasons for quitting, and videos of close friends/relatives motivating them to quit), access to the materials in pdf format that were provided during the sessions, and the possibility of self-reporting tobacco use. They will receive notifications to encourage and support a new quit attempt during this follow-up phase (Figure 4).(c)*Smokers*: behavioral and cognitive advice to quit (tips), the possibility of setting a quit date in a calendar, notifications consisting of strategies to be prepared for cessation, strategies to cope with cravings (distraction tools, such as gifs, games, or videos; and social-support-seeking strategies, such as access to an emergency contact list), motivational strategies (list of personal reasons for quitting, personal video with reasons for quitting, and videos of close friends/relatives motivating them to quit), access to the materials in pdf format that were provided during the face-to-face sessions, and the possibility of self-reporting tobacco use. Likewise, they will receive notifications to encourage a quit attempt during this follow-up phase (Figure 5).

The SinHumo App was developed by a team of psychologists, researchers, and computer programmers as an evidence-based App to complement a cognitive–behavioral intervention. Regarding the development of the SinHumo App, firstly, a review of available smoking cessation Apps literature was conducted to examine the main features and outcomes of existing Apps to quit [21]. Then, expert meetings were scheduled to design the components and features of the App, based on the extracted information. The App components integrate practice guidelines for treating tobacco use and dependence [29], and principles of behavior change techniques [30]. Finally, the usability and performance of the application was tested in a group of smokers.

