#### 2.4.2. Cognitive Behavioural Smoking Cessation Intervention and Control App (Control Condition)

The cognitive–behavioral psychological treatment applied in this condition is identical to the one described above in the experimental condition, but with a control App (Table 1 and Table 2). This App will be used during the treatment sessions (Phase 1) and follow-up period (Phase 2), with only two basic contents: a smoking self-report tool, and access to the written materials in pdf format provided during the face-to-face sessions.

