**Figure 5 ijerph-19-09770-f005:**
[figure not shown]
SinHumo App features during phase 2 for relapsers and smokers.

**Table 1 ijerph-19-09770-t001:** Summary of session-by-session outline of intervention procedures and App components (Phase 1) in the experimental and control conditions.

	Experimental Condition (SinHumo App)	Control Condition (Control App)
Session1	Overview of treatment and App usage Smoking cessation treatment rationale Review cigarette self-monitoring using the App (tracking cigarettes smoked, pleasure experienced, and smoking antecedents and consequences) Automatically generated cigarettes consumption graph available in the App Discussion of reasons for smoking and for quitting and completion tool available in the App named “reasons to quit” Discussion about smoking history and past quit experiences Explanation of written materials included in the App about tobacco, nicotine dependence, smoking health consequences, and cessation benefits Explain nicotine fading through brand change and set weekly cigarette reduction goals using the App tool Intersession activities: - Brand change - Communicate to at least one person (family, friend, coworker, etc.) that he/she is trying to quit smoking in the next 30 days - Not smoking more cigarettes than the average of those smoked the previous week - Leave a third of the cigarette without smoking - Refuse cigarette offers Intersession motivational notification through the App	Overview of treatment Smoking cessation treatment rationale Review cigarette self-monitoring using the App (tracking cigarettes smoked, pleasure experienced, and smoking antecedents and consequences) Discussion of reasons for smoking and for quitting Discussion about smoking history and past quit experiences Explanation of written materials included in the App about tobacco, nicotine dependence, smoking health consequences, and cessation benefits Explain nicotine fading through brand change Intersession activities: - Brand change - Communicate to at least one person (family, friend, coworker, etc.) that he/she is trying to quit smoking in the next 30 days - Not smoking more cigarettes than the average of those smoked the previous week - Leave a third of the cigarette without smoking - Refuse cigarette offers

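### Both arms are treated in therapy groups, but the sample size and the abstinence model treat participants as independent, so any positive within-group correlation makes the primary test anti-conservative and the stated power optimistic

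*Protocol article*

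**What the plan says.** - **Delivery.** Section 2.4.1, on the experimental condition: "This intervention is applied in a group format and consists of 8 one-hour sessions once a week". Section 2.4.2, on the comparison arm: "The cognitive–behavioral psychological treatment applied in this condition is identical to the one described above in the experimental condition, but with a control App". Both arms are therefore treated in groups.
- **Allocation.** The Abstract says: "Participants will be randomized to one of two conditions, using a 1:1 allocation ratio". Nothing in the article describes therapy groups being randomized, or how they are formed.
- **Session content.** Table 1 sets out each session separately for the two arms. Only the experimental column has goal-setting with the App tool, the automatic consumption graph, and compliance checks made through the App.
- **Sample size.** Section 2.3 assumes 50% against 30% abstinence at 12 months, 90% power and alpha 0.05, and concludes that "a minimum of 99 participants per group will be required". With 25% attrition this becomes 132 per arm, 264 in total. No group size, ICC or design effect appears.
- **Analysis.** Section 2.11: "Logistic regression analyses adjusted for baseline characteristics (i.e., sex, age, education level) will be carried out to examine whether abstinence rates differ significantly". No therapy-group or therapist effect is mentioned. Multilevel modelling is named for another purpose: "Multilevel and survival analysis will also be carried out to examine the relapse process". Its levels are not stated.

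**The concern.** People who spend eight weekly sessions in one group share a therapist, peers and a period of calendar time. Table 1 shows that the sessions rely on discussion and social support. Their later abstinence may therefore be correlated. Randomizing individuals does not remove this, because the correlation arises after randomization. Baseline covariates such as sex, age and education do not absorb it.

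If each group lies within one arm, variation between groups adds to the variance of the arm comparison. A logistic regression that assumes independent observations leaves that part out, so its standard error is too small. At stake are the type I error of the primary comparison, the width of its confidence interval, and the power on which 264 participants were chosen.

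**Working it through.** **Inputs from the article:** 50% and 30% abstinence, 90% power, alpha 0.05 (sidedness not stated), 99 analysed and 132 randomized per arm, 25% attrition, and all randomized participants in the primary analysis (sections 2.3 and 2.11).

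**Assumptions, not in the article:** m = 8 to 10 participants per group, ICC = 0.01 to 0.05, and groups nested within arm.

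**1. Reproduce the stated sample size.** Two independent proportions, unpooled variance, n = (z_alpha + z_beta)² × (0.5×0.5 + 0.3×0.7) / 0.2².
- One-sided alpha 0.05: (1.645 + 1.282)² × 0.46 / 0.04 = 98.5, so 99.
- Two-sided alpha 0.05: (1.960 + 1.282)² × 0.46 / 0.04 = 120.8, so 121.
- Attrition: 99 / 0.75 = 132.

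The figure of 99 is reached exactly with one-sided alpha and no design effect.

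**2. Design effect.** DE = 1 + (m − 1) × ICC.
- m = 8, ICC = 0.01: 1 + 7 × 0.01 = 1.07.
- m = 10, ICC = 0.05: 1 + 9 × 0.05 = 1.45.

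The true standard error is √DE times the one computed under independence: 1.034 and 1.204 times.

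**3. True error of a nominal two-sided 5% test that ignores groups.** 2 × [1 − Φ(1.96/√DE)].
- DE 1.07: 5.8%.
- DE 1.45: 10.4%.

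If 25% attrition also shrinks the analysed groups, m becomes 6 to 7.5, DE is 1 + 5 × 0.01 = 1.05 to 1 + 6.5 × 0.05 = 1.325, and the error is 5.6% to 8.9%.

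**4. Power of a test that holds its level.** Φ(0.2/√(0.46/n_eff) − z_alpha), with n_eff = n/DE. For n = 99, n_eff is 93 at DE 1.07 and 68 at DE 1.45. Each row has its own unclustered baseline.

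| Basis | No clustering | DE 1.07 | DE 1.45 |
|---|---|---|---|
| 99 per arm, one-sided (the basis that gives 99) | 90.1% | 88.3% | 78.6% |
| 99 per arm, two-sided | 83.5% | 81.0% | 68.3% |
| 132 per arm, two-sided, same 50%/30% rates | 92.3% | 90.6% | 80.3% |

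The loss due to clustering, read along each row, is about 2 to 11.5 points (90.1 − 88.3 and 90.1 − 78.6), 2.5 to 15 points (83.5 − 81.0 and 83.5 − 68.3), and 2 to 12 points (92.3 − 90.6 and 92.3 − 80.3).

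**The case against.** **A condensed article may leave this to the SAP.** Random effects and robust variances often are left there, the covariates read as examples, and omitting a group term is not the same as ruling one out. This has some force for the model. It has less for the sample size, which is fixed at a value with no room for a design effect. The article also names the abstinence model and what it adjusts for, and assigns multilevel analysis to relapse.

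**Nesting within arm is inferred.** This stands. Table 1 makes it the natural reading, since mixed groups would show control participants the experimental App tools, but no section states it. If groups mixed both arms, the standard error would not be too small in this way. The same holds for therapists: the article does not say whether they serve both arms, and if they do, a shared therapist would not inflate the variance of the arm effect in the same way.

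**The correlation may be small.** The primary outcome is measured 12 months after the sessions end, and nothing in the article shows how much within-group correlation remains. At ICC 0.01 in groups of 8 the error is 5.8%, a minor departure. This limits the size of the problem, not its direction.

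**The intention-to-treat set is larger than 99.** Section 2.11 includes everyone randomized. With 132 per arm at the planned rates, two-sided power still exceeds 90% at the low end of the range (90.6%). The rates would fall if missing participants were counted as smokers, so this is a partial rescue. It does nothing for type I error, because a model without clustering is anti-conservative at any sample size.

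**A stronger reading to avoid.** A reader might set the planned 90% beside 68.3% and blame clustering for the whole gap. The figures do not support that. Two-sided power at 99 per arm is already 83.5% with no clustering, because 99 comes from a one-sided calculation. That is a separate question about the sidedness of alpha.

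**Conclusion.** The point holds in conditional form. Group delivery in both arms, a sample size without a design effect, and an abstinence model described without a group term are all in the article. Given groups nested within arm and a positive ICC, the direction is certain: standard errors are too small and power is overstated. The article does not establish that the ICC is positive at 12 months, so the error rate cannot be called inflated as a matter of fact.

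The size rests on the assumed group size and ICC. Over the range used, it runs from negligible (error 5.6% to 5.8%, about 2 points of power) to material (error 8.9% to 10.4%, some 11 to 15 points of power at the larger design effect, depending on the basis). Because the upper end affects the validity of the primary test and the correction is cheap, it is worth making while recruitment continues (section 2.10).

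**What to change.** - Record the therapy-group identifier and the therapist for every participant, and state how groups are formed and whether each belongs to a single arm.
- Make the 12-month primary model a mixed-effects logistic regression with a random intercept for therapy group, or GEE clustered on therapy group with a small-sample correction, keeping the same covariates.
- Use the same approach for the other between-arm abstinence outcomes.
- Restate power over a stated range of group size and ICC, against an explicit unclustered baseline with the sidedness of alpha given.

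The cost is one or two data fields and revised analysis wording. Intervals become slightly wider and the stated power less favourable. No additional participants are needed.
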